## Abstract

Prior studies suggest that visual functions undergo time-of-day variations. Under naturalistic entrainment, diurnal changes in physiology may be driven by circadian and/or homeostatic processes, and repeated measurements at different times of day are thus not suitable to draw unambiguous conclusions about circadian effects on visual function. In this study, we disentangle circadian and homeostatic effects on variations of retinal function. We examine the earliest stages of image-forming (temporal contrast sensitivity of the post-receptoral channels) and non-image forming visual functions (pupillary light response) by employing a short forced-desynchrony multiple-naps protocol lasting 40 hours. Participants (n = 12, 50% female) will stay in a controlled time-isolating environment under dim-light conditions and adhere to an ultra-short sleep-wake cycle, alternating between 2h30m of wake time in dim light and hour of sleep in no light. During eleven intervals of wakefulness, participants will undergo psychophysical and pupillometric assessments with silent-substitution stimuli. We hypothesize that the sensitivity of retinal mechanisms undergoes circadian variations. This hypothesis will be investigated by separately determining psychophysical contrast thresholds to silent-substitution stimuli targeting the post-receptoral (consistency) pathways (isoluminant red-green, L–M; isoluminant blue-yellow, S; luminance, L+M+S). We will furthermore measure the pupillary light response to peripheral stimuli (annulus 10^∘^–30^∘^) in comparison to the response to stimuli isolating or including melanopsin stimulation. All stimuli will be delivered at constant retinal irradiance using a Maxwellian view system or artificially restricting pupil size. Additionally, we will quantify and report effects of our test stimuli on the circadian system by comparing the dim light melatonin onset (DLMO) timing during two supplementary evening sessions, comparing dim-light conditions to such with experimental light exposure. Our work informs the fundamental biological mechanisms underlying the influence of light on the human circadian system. Based on our findings, current models about the sensitivity of the circadian system may need to be modified in order to account for the bidirectional influence of circadian function and photoreception.

## 1 Introduction

### 1.1 Processing of light in the retina

Exposure to light enables vision and visual perception, allowing us to see the world in its colourful and spatial detail [1]. Additionally, light exposure also influences our physiology and behaviour through circadian synchronization [2], melatonin suppression [3–6] and modulation of alertness [6].

The pathways underlying these distinct functions are also anatomically distinct and separated into image-forming and non-image-forming pathways. Signals in both pathways arise from the three classes of photoreceptors in the retina: rods, cones and the melanopsin-containing intrinsically photosensitive retinal ganglion cells (ipRGCs). Image-forming signals primarily stem from rods and three types of cones with different spectral sensitivity. Phototransduction takes place at the photoreceptor level, but before the resulting signal is passed on to the retinal ganglion cells and eventually subcortical (lateral geniculate nucleus; LGN) and cortical targets (primary visual cortex; V1), the signal is recombined through retinal wiring. The coding of luminance is based on the summation of L- and M-cone signals, and two opponent channels encode colour: the red-green channel that is driven by the antagonism of L-cone versus M-cone signals (L-M), and the yellow-blue channel driven by the S-cone versus the sum of L- and M-cone signals (S-[L+M]) [7]. The ipRGCs represent a subset of retinal ganglion cells which express their own photopigment, melanopsin. In addition to this intrinsic photosensitivity, they also receive synaptic input from the rods and cones.

The effects of light on human circadian and neuroendocrine physiology are orchestrated by the suprachiasmatic nucleus (SCN) in the hypothalamus. Through the retinohypothalamic pathway, which relays information from the retina to the hypothalamus, the SCN encodes light to synchronize the internal circadian rhythm to the external environment, rendering light input an important circadian signal [8]. Given the widespread influence of the central pacemaker in many physiological systems and tissues, and peripheral clocks in other tissue types, it is highly likely that one or all sites of the input pathway is also affected by a circadian modulation.

Across the day, light exposure has different and opposing circadian effects depending on the timing of exposure. Given by the phase response curve (PRC) to light, light exposure in the morning advances the circadian phase while evening light exposure will cause a delay [9–11]. To what extent the PRC is driven by a modulation of sensitivity in the retina or mechanisms along the retinohypothalamic pathway is unknown. Some studies have investigated how the pupillary light reflex (PLR) is modulated, as it reflects the response of all photoreceptors to light [12,13]. They revealed that there are time-of-day differences in melanopsin-mediated pupil responses [14,15], indicating that at least some variability arises and is measurable as early as in the retina. Indeed, if this were the case, i.e., that there is a circadian “gating” of the retinal signal, it could explain the effects seen downstream. Only a few studies have documented the diurnal variation of basic visual functions, such as luminance perception, including temporal contrast [16] and spatial contrast sensitivity [17]. Some studies have also investigated diurnal variations in colour vision [17,18]. Additionally, there is strong evidence for diurnal variations of interocular pressure and corneal thickness, which could lead to differences in retinal function [19,20].

However, the emerging pattern of results is somewhat heterogeneous, and does not factor in that time-of-day variations in retinal and physiology cannot be uniquely attributed to the circadian clock. The goal of this study is to characterise the variability of retinal functions as a function of circadian phase.

### 1.2 Disentangling circadian and homeostatic process

The intercorrelated nature of processes controlled by the circadian clock and behavioural rhythms poses considerable challenges to the investigation of uniquely circadian effects, requiring well-controlled studies spanning many hours to multiple weeks. Briefly, daily variation in human physiology, behaviour, and experience at the 24-hour scale are governed by two independent processes, an endogenous circadian rhythm and a sleep homeostat [21,22]. Under normal, entrained conditions, these processes are working in tandem to regulate the propensity for sleep, and to create regular cycles of sleep and wakefulness.

The two-process model postulates that the homeostatic “process S” gradually increases during periods of wakefulness, giving rise to an increasingly stronger drive for sleep the longer one stays awake, and affecting a variety of physiological and cognitive functions. During sleep, sleep pressure decreases exponentially, allowing for recovery and restoring balance before the next sleep-wake cycle. At the same time, the circadian “process C” regulates various physiological functions and signals, which in interaction with the sleep homeostat influence sleep timing and propensity. Under entrained conditions, the sleep-wake cycle is consequently aligned with the internal body clock and external environmental cues, making both processes correlated with one another [23].

In the laboratory, it is possible to disentangle their effects on neurobehavioural functions by systematically manipulating sleep timing, sleep duration and contextual factors such as ambient light, temperature and food intake. There are various within-person study designs that requiring repeated measurements of outcome parameters and careful monitoring and controlling of circadian signals and homeostatic influences [23–25].

### 1.3 Ultra-short sleep-wake forced-desynchrony protocol

Here, we will employ a 40-hour forced-desynchrony (FD), multiple-naps protocol with a night-day/light-dark (LD) cycle totalling 3h45m. In this protocol, sleep pressure is kept at a constant low level by rapidly alternating between sleep and wake periods (i.e. regular naps). Other homeostatic influences like food intake and activity will be adapted to the ultra-short rhythm. External influences including ambient temperature and dim light during wakefulness are kept constant to minimize the influence on the circadian rhythm.

In the literature, a similar protocol has been successfully implemented before, scheduling sleep and wake time in a 2:1 ratio of imposed day length of 3h45m [26,27]. 150 min (2h30m) wake intervals in dim light (< 10 lux) provide opportunity for measurements and are followed by 75 min (1h15m) sleep intervals in darkness. The protocol lasts 40 hours, yielding 11 repeating light-dark (LD) cycles or measurement blocks.

This study will isolate circadian effects on early stages of visual processing from homeostatic effects with a short forced-desynchrony protocol. Participants will stay in the laboratory for 40 hours, which will cover, on average, 1.5 circadian periods.

They will adhere to an ultra-short sleep-wake rhythm schedule, comprised of 2h30m (150 minutes) of wake time and 1h15m (75 minutes) of sleep opportunity. During each scheduled instance of wakefulness, a series of (psycho-)physical parameters will be measured in order to determine sensitivity of photoreceptor mechanisms, circadian phase, sleep pressure, and other possible physiological outcomes assumed to undergo circadian change. Specifically, we will repeatedly collect data on: (1) psychophysical performance, and more specifically temporal contrast sensitivity (tCS) (2) the immediate maximum pupil constriction amplitude (pupillary light response, PLR) to carefully crafted light stimuli, (3) intra-ocular pressure, (4) structural properties of the cornea and retina (5) salivary melatonin concentration, (6) mood, and (7) sleepiness; additionally, there will be continuous measurements of physiological functions (8) temperature in the core body and the proximal-distal gradient of skin temperature, (9) heart rate variability via electrocardiography (ECG), and (10) interstitial glucose concentration.

### 1.4 Hypotheses

Building upon prior evidence for a time-of day dependency in image-forming (i.e., luminance and colour perception) and non image-forming functions (i.e., pupillary light response), we hypothesize that photoreceptor sensitivity and retinal mechanisms are modulated by the circadian rhythm.

Our hypotheses regarding variations in non-image forming function investigate circadian effects in the pupillary light reflex to different conditions.

The detailed confirmatory hypotheses state that the PLR shows circadian effects in the response to

modulation of the colour opponent process L-M with constant activation of S and melanopsin (L–M) [H1a];modulation of the S-cones with constant activation of L-cone, M-cone, and melanopsin activation (S) [H1b];joint modulation of L-, M-, and S-cones (L+M+S) [H1c];selective modulation of melanopsin activation (Mel, constancy of cone activation) [H1d].

To investigate circadian effects isolated from homeostatic effects in the image-forming pathway by evaluating temporal contrast threshold to two different frequencies, focusing on the following photoreceptor mechanisms using silent-substitution stimuli: activation of the luminance channel (L+M+S), post-receptoral red-green channel (L–M), activation of the S-cones (S-(L+M)), activation of melanopsin-driven signaling in ipRGCs. We will evaluate the contrast sensitivity to:

modulation of the colour opponent process L-M with constant activation of S (L–M*) [H2a];modulation of the S-cones with constant activation of L-cones and M-cones (S*) [H2b];joint modulation of L-, M- and S-cones (L+M+S*) [H2c],

with none of the conditions controlling for melanopsin modulation, as indicated by the asterisk. The hypotheses regarding psychophysical performance in image-forming vision, relates to two different frequencies, yielding six different hypothesis: each hypothesis will be investigated for a low frequency (2 Hz) and a high frequency (8 Hz) to identify and possible explore differences based on temporal sensitivity.

### 1.5 Prospective impact of the study

We will characterise circadian influences on photoreceptor sensitivity and sensitivity of post-receptoral mechanisms, thereby gaining further insights into mechanisms and extent of variations of visual performance. Studying circadian dependency in human visual function will deepen our mechanistic understanding of the link between image-forming and non-image-forming functions. Furthermore, our results have practical implications for professional contexts that involve driving or rely on colour discrimination and thus require high visual performance, and is of particular importance when circumstances impose circadian disruption and sleep disruption, such as in the medicine, aviation or military service. Finally, from a clinical perspective, the localisation of circadian variation in eye physiology may also have implications for the treatment and management of eye conditions such as glaucoma.

## 2 Methods

### 2.1 Study sample

In this study, we will recruit and enrol twelve healthy participants aged 18–35 years (target 50% female) with no ocular and retinal diseases, no psychiatric or neurological diseases, with normal sleep-wake behaviour, normal colour vision, and matching all criteria listed in Table 1 and not matching any criteria listed in Table 2.

**Table 1 pone.0300405.t001:** Inclusion criteria.

Domain	Assessment method	Criterion	Time of Screening
Age	Self-report	≥18 years	Online screening
		≤35 years	
Physical health	Self-report	Good physical health	Online screening
Mental health	Self-report	Good mental health	Online screening
Ocular health	Ophthalmological examination	Good ocular health	In-person screening
Visual acuity	Landolt C	Normal or corrected-to-normal vision	In-person screening
Colour vision	HRR Pseudoisochromatic Plates (4th edition)	Normal colour vision	In-person screening
Sleep and circadian regularity	Self-report	Preference of high ranking participants	Online screening
Hormone status	Self-report	Women and men without any hormonal disorders; women with or without hormonal contraception	Online screening

**Table 2 pone.0300405.t002:** Exclusion criteria.

Domain	Assessment method	Criterion	Time of screening
Body mass index (BMI)	Calculated based on body weight in everyday clothes without shoes and height	<18.5 or >25	In-lab screening
Substance abuse	Self-report, AUDIT	AUDIT >7	Online screening
Depressive symptoms	Self-report		In-lab screening
History of anxiety disorder	Self-report		In-lab screening
Extreme chronotype	Self-report, MCTQ (MSF-SC)	<2:00 or >5:30	Online screening
Medication use	Self-report	Any use of medication (except for hormonal contraception)	Online & in-lab screening
Smoking	Self-report	Habitual smoking	Online screening
Photosensitive epilepsy	Self-report	Diagnosis of epilepsy	Online & in-lab screening
Shift work	Self-report	No shift work in the past 3 months	Online screening
Transmeridian travel	Self-report	No inter-time zone travel >2 time zones in the past 3 months	Online screening
Pregnancy	Self-report, HCG urine test	Positive result	Online screening
Endocrine alterations	Self-report		Online screening
Drug use	AMP, BZD, COC, MOR/OPI, THC pane	Positive result	Light exposure session & forced desynchrony session
Alcohol use	Breathalyser	>0.0%	Light exposure session & forced desynchrony session

#### 2.1.1 Recruitment.

We will recruit participants using a multi-modal strategy using flyers, posters, mailing lists and other outlets, word-of-mouth and advertisements placed on the internet. The first point of contact will be an online screening. Upon completion of the online screening, their suitability for the study will be determined automatically, followed by an invitation or removal from the participant pool. Participants will undergo a thorough in-laboratory screening described in Sect 2.4.1. During screening, formal criteria for participation will be checked again with regard to their physical health and psychological stability. Participants will be informed about the study protocol and experimental procedures, and given opportunity to ask questions before giving written consent.

#### 2.1.2 Remuneration.

Participants will be remunerated for their time. There will be two in-laboratory evening sessions followed by an adaptation night in the lab (more details in Sect 2.4.2). For each of the evenings, participants will be compensated with €30 plus €20 for the adaptation nights. The second evening session and adaptation night will be immediately followed by the forced-desynchrony protocol starting in the morning. For the forced-desynchrony session of 40 hours, they will receive a compensation of €400. Participants may leave at any point upon request, or will be excluded in case of reduced compliance to an extent that renders the data deficient. When returning the actigraph, participants will be rewarded €20. As participants are incentivised to provide complete data for actimetry and the sleep diary, they will be rewarded an additional €80 if less than 20% of data is missing. The maximum remuneration is therefore €600.

#### 2.1.3 Sample size.

This study will follow a within-person design. Each participant provides eleven repeated measurements. We will determine evidence for our hypotheses using a sequential Bayesian sampling strategy, such that data collection will continue until evidence strength suffices, or until a maximum of twelve participants. This maximum sample size is set by resource limitations. For the sequential sampling strategy, we will use Sequential Bayes Factor (BF) of the statistical model testing circadian modulation of melanopsin-dependent pupil constriction. The stopping criterion is BF > 10 or BF < 1/10 to quantify evidence strength for or against a circadian effect.

### 2.2 Study design

The study is set up to be a within-participant design. We will invite one participant at a time. Each participant will take part in one evening session a week after starting a circadian stabilisation phase, then come in for another evening session that is followed by an adaptation night and the subsequent completions of the forced-desynchrony protocol, which encompasses 11 measurement blocks and spans 40 hours. Each measurement block encompasses various measurements. The order of measurements is constant between participants. In the pupillometric measurements, experimental conditions, i.e. direction of post-receptoral stimulation, will be counterbalanced between participants, while for the psychometric measurements, the order of experimental conditions will be fixed, while frequency conditions are randomised.

Repeating measurement blocks are interspersed with sleep opportunities to prevent sleep deprivation, thus systematically shortening a typical sleep-wake cycle from approximately 24 hours to 3h45m. During one period of 24 hours, participants will thus complete 6.4 sleep-wake cycles. Additionally, throughout the entire study period, participants will provide a combination of regular ambulatory measurements and experience sampling starting up to two weeks before the measurements. Our study design as shown in Fig 1 will yield longitudinal data spanning up to three weeks.

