#### 2.4.4 In-laboratory visits.

During the forced-desynchrony session, participants will repeatedly undergo a battery of visual, physiological and psychometric tests during wakefulness. The experiments that will be administered during one repeatable block are described in Fig 3 and detailed below.

*Compliance during in-laboratory visit.* The experimenter will continuously monitor compliance and the successful completion of experiments. Given the demanding nature of the protocol, there is tolerance for participant’s failure to perform in individual tests. A block’s data is considered for analysis as long as one test repetition within that block is successful. However, experimentation will proceed across all modalities using light-emitting devices, even if data collection issues occur in a single modality. These devices serve a dual purpose: not only do they measure visual outcomes, but they also provide consistent light exposure > 10 lux, which is important for maintaining comparability between participants. If the experimenter fails to collect data from both primary modalities – pupillometry and psychophysics – for more than one block due to any reason (e.g., non-compliance, fatigue, tiredness), the experimental session may be aborted. This is because the increased measurement intervals would render the data unsuitable for testing circadian hypotheses.

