*Experimental procedure.* During the forced-desynchrony session, every participant then completes 11 blocks, with a test and a test repetition in each block. Each test encompasses an adaptation period and 25 trials. Participants adapt to a photopic background ($60\;{cd/m}^{2}$) for four minutes, to ensure rod saturation. The adaptation period is followed by 25 trials per test, where participants will view sinusoidal light modulations with a frequency of 0.4 Hz, interspersed with white baseline stimulation. 0.4 Hz was selected to measure pupil responses in a temporal regime in which all photoreceptors are likely responsive [13]. The experimental stimulus presentation takes place for five seconds, followed by a period of baseline stimulation with white light of 13 seconds, yields a total trial duration of 17 seconds. One test consists of 25 trials, five repetitions of each experimental condition; conditions are counterbalanced using an m-sequence. One test takes about 12–15 minutes, amounting to about 30 minutes per block for pupillometric assessment. A short break temporally separates the two tests.

*Control for rod intrusion.* As recent literature as shown that rods phototransduction may recover even at high light levels and based on temporal modulation [50,51], we will conduct a control experiment to test whether rods escape saturation. The control experiment will take place after data collection of the main study has been completed and will include a different set of participants than the participants in the main trial. Using pupillometry, we will evaluate the response to silent substitution stimuli targeting rods at light levels comparable to the planned experimental condition and with the same temporal frequencies. The results of this control study will be reported and discussed in the context of the results seen in the main study in subsequent publications.

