*Silent substitution of post-receptoral mechanisms.* We will probe the sensitivity for luminance and of the colour-opponent processes by means of (1) joint modulation of all three cones to target the luminance channel (L+M+S*), (2) isolated modulation of S-cones keeping the luminance channel constant (S*), and (3) antagonistic modulation of L- and M-cones to target the red-green channel (L–M*). The asterisk in condition labels indicates the lack of control over melanopic stimulation with the RGB monitor compared to the 6-LED stimulation device employed during pupillometry, e.g. S* is the S-cone isolating condition on the RGB monitor, where melanopsin activation cannot be kept at a constant level, while S is the S-cone isolating condition fixing L-, M-, and melanopsin-activation while modulating S activity. Maximum contrasts are predefined by the given colour gamut of the monitor (L+M+S*: 100%, S*: 51%, and L–M*: 6%) and starting values are partly lower as a trade-off between experiment length and visibility of the stimuli (L+M+S*: 90%, S*: 35%, and L–M*: 6%). The accidental activation of melanopsin will not be monitored. Effects of ipRGCs on the psychophysical tasks performance are assumed to be minimal.

*Post-receptoral temporal contrast sensitivity.* In the two-alternative forced choice (2AFC) tasks, stimulus contrast varies according to a staircase method, approaching the participant’s contrast threshold in relative steps. Contrast sensitivity is calculated from the threshold values. Within one test of the tCS task, different temporal frequencies, 2 and 8 Hz, are presented in interleaved order for one condition or photoreceptor mechanism. Participants determine whether the stimulus appears right or left from the centre of the screen with a left or right button press. Location varies randomly. After completion of three conditions, we will reiterate over the conditions twice, yielding nine tests per block. During the light exposure session (Sect 2.4.2), the participant will learn the task procedure, completing all 9 tests to achieve comparable light exposure levels. Tests are expected to last longer due to unfamiliarity in the light exposure session.

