#### 2.5.1 Image-forming visual function.

The image-forming pathway is investigated using psychophysical tests, testing of contrast thresholds. During the tCS task, the contrast threshold is determined; contrast is measured in percent. We will average the contrast threshold block-wise across test repetitions, separate for each condition. A linear mixed model will be used to investigate hypotheses H2a to H2c. Our primary outcome variable is the point estimate for the temporal contrast sensitivity in each test for a specific post-receptoral mechanism and a specific frequency. The temporal contrast sensitivity is the inverse of the contrast threshold determined by a two-up-one-down staircase method.

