Similarly, circadian modulation of psychophysical performance is assessed by testing for a circadian component in temporal contrast sensitivity *T*. The null model T(t) and the full model $T_{\tau_{j}}(t)$ are defined as in eqs (3) and (4) above. Model comparisons are conducted separately for low (2 Hz) and high (8 Hz) frequencies. While sensitivity differences between post-receptoral mechanisms are well-documented, there is currently no evidence to suggest frequency-dependent differences in circadian modulation. For the sake of parsimony, if results between low and high frequencies or across post-receptoral mechanisms differ, we will perform exploratory analyses. We will not enter sex, age, or demographic variables in our confirmatory analysis, as we do not see sufficient empirical evidence for confounding effects.

We will sample from the posterior distributions to obtain parameter estimates and derive amplitude (*A*) and phase angle (ϕ) of the proposed underlying circadian rhythm with

$$A=\sqrt{a^{2}+b^{2}}$$
(5)

and

$$\phi =\left\{ \begin{array}{cc} \arctan(\frac{-b}{a}), & a>0\\ \arctan(\frac{-b}{a})+\pi , & a<0\text{ and }b\geq 0\\ \arctan(\frac{-b}{a})-\pi , & a<0\text{ and }b<0\\ -\frac{\pi }{2}, & a=0\text{ and }b>0\;\\ +\frac{\pi }{2}, & a=0\text{ and }b<0\; \end{array}\right.$$
(6)

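### The three psychophysical mechanisms run in one fixed order, so place within each pass coincides with mechanism and a phase-dependent warm-up or fatigue effect would load on them unequally

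*Protocol article*

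**What the plan says.** Section 2.2 (Study design) states that "The order of measurements is constant between participants". It has pupillometric conditions counterbalanced between participants, "while for the psychometric measurements, the order of experimental conditions will be fixed, while frequency conditions are randomised". Section 2.4.5 adds that within a pupillometry test "conditions are counterbalanced using an m-sequence".

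For psychophysics, section 2.4.6 states: "After completion of three conditions, we will reiterate over the conditions twice, yielding nine tests per block". The two frequencies are "presented in interleaved order for one condition or photoreceptor mechanism", so frequency is not tied to test position.

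Section 2.5.1 then states: "We will average the contrast threshold block-wise across test repetitions, separate for each condition". Test position therefore drops out of the analysed block value. The models of section 2.6.2 compare a sine-cosine model with a constant level and contain no position or time-on-task term. The same section says that "if results between low and high frequencies or across post-receptoral mechanisms differ, we will perform exploratory analyses". Under section 2.4.4 a block "is considered for analysis as long as one test repetition within that block is successful".

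Two points are read from context. The contrast within the section 2.2 sentence implies that the fixed order is the same for every participant. Section 2.4.6 implies, without saying so, that each pass repeats that order. It lists the mechanisms but does not give their running order.

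**The concern.** H2a to H2c are separate claims about the red-green, S-cone and luminance mechanisms, and sections 2.6.2 and 2.6.3 foresee exploring differences between them. With one order for everyone, the same mechanism opens every pass and the same one closes it, in all 11 blocks.

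An order effect of constant size is harmless, because it shifts the mean level of a mechanism and not its rhythm. An order effect that changes with circadian phase is different. Examples are a slower start, or a steeper loss over the test series, at some phases. It would enter the three mechanisms in unequal amounts and in the same direction in every participant, so averaging over people would not reduce it. The protocol itself regards alertness as something that may vary across blocks: section 2.4.8 records sleepiness and vigilance in every block, and section 2.4.4 allows for failures from fatigue.

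At stake is whether a rhythm seen in one mechanism but not in another can be attributed to the mechanism.

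**Working it through.** **1. Reproducing the plan's count.** 3 mechanisms × (1 + 2 repeats) = 9 tests per block, as section 2.4.6 states.

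**2. Positions under a repeated fixed order.**
- First mechanism: 1, 4, 7; mean 4.
- Second mechanism: 2, 5, 8; mean 5.
- Third mechanism: 3, 6, 9; mean 6.

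Share of position variance explained by mechanism: Σ 3(mean − 5)² / Σ (p − 5)² = 3(1 + 0 + 1)/60 = 0.10. Running each mechanism as one set of three (means 2, 5, 8) would give 3(9 + 0 + 9)/60 = 0.90, and complete aliasing would be 1. Place within a pass (first, second, third) is completely aliased with mechanism.

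**3. Leakage into the rhythm.** Let the position effect be w(p) multiplied by a circadian oscillation of unit amplitude. The spurious amplitude for a mechanism is the mean of w over its three positions. The protocol gives neither the shape nor the size of w, so the shapes below are assumptions.

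| Assumed w(p) | 1st | 2nd | 3rd | Largest difference | Each, if order balanced |
|---|---|---|---|---|---|
| Linear fatigue, (p − 1)/8 | 0.375 | 0.500 | 0.625 | 0.25 | 0.50 |
| First test only | 0.333 | 0 | 0 | 0.33 | 0.11 |
| Warm-up, exp(−(p − 1)) | 0.351 | 0.129 | 0.047 | 0.30 | 0.18 |
| Warm-up, exp(−(p − 1)/3) | 0.501 | 0.359 | 0.257 | 0.24 | 0.37 |

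Example, linear fatigue: (0 + 3 + 6)/24 = 0.375 for positions 1/4/7. A noise-free fit to 11 blocks 3.75 h apart, with a 24 h period, returns these amplitudes. It returns 0 when the position effect is the same in every block.

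**4. If repetitions are lost.** If only the first pass of a block succeeds, the positions are 1, 2 and 3, and mechanism and position coincide completely in that block.

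**5. What this could do to the Bayes factor (illustration only).** Assumptions: 12 participants, 11 blocks, SD 0.15 log10 unit per test, no true rhythm, same phase in everyone, common sine and cosine terms without random slopes. With 12 × 11 = 132 block values and two extra parameters, the BIC approximation is BF = exp(LR/2)/132.

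- *First test only, swing of 0.10 log unit.* Fixed order: BF > 10 in roughly 29% to 40% of simulated studies for the first mechanism, depending on implementation, and at most about 0.3% for the other two. Rotated order: about 1% for each. At a swing of 0.05 the first mechanism reaches only 3% to 4%.
- *Linear fatigue, 0.02 log unit per test at the worst phase and none at the best.* The slope oscillates with amplitude 0.01, so the expected amplitudes are 0.01 × (4 − 1), 0.01 × (5 − 1) and 0.01 × (6 − 1) = 0.03, 0.04 and 0.05. Fixed order: BF > 10 in about 20% to 28%, 47% to 64% and 78% to 91% for the first, second and third mechanism. Rotated order: about 46% to 66% for each.

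**6. Can a model separate position from mechanism?** A test-level design with mechanism, linear position and a first-test indicator, each crossed with (1, cosine, sine), has 9 + 3 + 3 = 15 columns and rank 15. Both effects in step 5 can therefore be estimated apart from mechanism. A free effect of place within a pass cannot, because its indicators are the mechanism indicators.

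**The case against.** The strongest defence is that each confirmatory test compares one mechanism with its own constant level within people, for which a fixed order is acceptable. Differences between mechanisms are labelled exploratory. The three passes already spread each mechanism over early, middle and late positions, all nine tests are practised in the light exposure session, and the naps are meant to keep sleep pressure low and constant. The harm needs an interaction of position with phase that nobody has shown here. The simulated rates also rest on assumed variances and leave out the random sine and cosine effects of eq. (4). A rough BIC penalty for those two variances lowers the first-test case at 0.10 from 38% to 8%, and the fatigue case to about 4%, 20% and 54%. All of this stands, and it limits the weight of the point.

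Three stronger readings are tempting, and the protocol does not support them:

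- *Mechanism is wholly confounded with position in the block.* It is not. The three passes leave mechanism explaining 10% of position variance. Only place within a pass and predecessor coincide with it.
- *No analysis could separate the two.* A test-level model can, for an effect whose form is specified correctly. Adding the matching position-by-phase term under the fixed order brought false BF > 10 down to about 0.5% or less in both simulated cases. This fails only for effects tied to place within a pass.
- *Rotation would make the H2a to H2c tests safe.* It helps when the effect is confined to the start of the block. Under linear fatigue it only shares the false rhythm equally, and the first mechanism does worse than under the fixed order.

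**Conclusion.** The point holds as a cheap improvement to the design. It is not a flaw that invalidates the confirmatory tests. The protocol balances condition order in one primary modality and fixes it in the other without giving a reason. Nothing in the analysed outcome or the models would reveal a position effect.

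If warm-up or time-on-task varies with circadian phase, the mechanisms would differ by about 0.24 to 0.33 of that effect under the shapes tried, in the same direction in all participants. The consequence falls mainly on statements that one mechanism has a rhythm and another does not. For a single hypothesis it matters most if the effect is confined to the first test of the block.

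This rests on two inferences (one order for everyone, repeated in each pass) and on assumed shapes. The absolute size cannot be derived from the protocol, which gives no variances.

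**What to change.** In sections 2.2 and 2.4.6, replace the fixed order with one that is rotated across participants, assigned in enrolment sequence and held constant within a participant over the light exposure session and all 11 blocks. There are two options:

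- **All six orders**, two participants each at 12. This balances place within a pass and predecessor.
- **The three cyclic orders** (1-2-3, 2-3-1, 3-1-2), four participants each at 12. This balances place within a pass only. Repeated over three passes, the cyclic orders leave every mechanism with the same predecessor.

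As a supplement, specify a test-level sensitivity model in section 2.6 that adds test position crossed with the sine and cosine terms. Fit it before interpreting differences between mechanisms. If participants have already been tested in the fixed order, this model is a partial remedy for their data, because it cannot isolate place within a pass.

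The cost is a sentence in the protocol and an order setting per participant. The same nine tests are run, so there is no added time and total light exposure stays comparable. Two limits should be stated. Rotation equalises a phase-dependent fatigue rhythm common to all mechanisms but does not remove it. Balance will be incomplete if sequential sampling stops before a full set of orders is reached. Order effects will also differ between people, which the random intercept and random sine and cosine effects can largely take up.
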